### Interventions

#### Breathing and Attention Training (BAT)

Participants are informed that they will be randomly assigned to either the Focused-Breathing and Attention Training or the Standard-Breathing and Attention Training. The consent form provides information that the Standard-BAT includes instruction on deep breathing and relaxation, and the Focused-BAT is similar to the Standard-BAT in most ways but includes extra instructions to help you focus and alter your breathing patterns. Thereafter, each intervention is referred to as BAT more generally to all participants in an attempt to evenly manage participant expectations and reduce potential placebo effects [102, 103, 121]. When first introducing the interventions to participants during Visit 2, they will receive the same information on the possible effects of BAT (see Additional file 1: Appendix 1).

Both interventions involve five separate, 17-min practice sessions of BAT. The first 12 min of both interventions include instructions to breathe in ways consistent with their assigned intervention, and both interventions include 5 min of silence at the end where participants are instructed to simply relax and lay still without modifying their breathing in any way. The interventions will be delivered via an audio recording in order to standardize the interventions across sessions and participants, thereby enhancing treatment fidelity through consistent intervention delivery. When practicing in-person, participants will remain reclined in a chair; when practicing at-home, participants will be instructed to lie down in a safe and comfortable position. Aside from the specific breathing instructions during the 12-min of BAT, all other aspects (e.g., setting, frequency, posture, facilitator) of the interventions will be identical [103, 104]. The scripts for each intervention are included in Additional file 1: Appendix 1.

#### Focused-BAT

Each session of the Focused-BAT intervention involves three rounds of conscious connected breathing and breath retention. For the breathing phase, participants are instructed to take about 40 deep connected breaths (no pause between inhale and exhale) at a rate of about 20 breaths per minute. The inhalation is encouraged to be deep into the abdomen (i.e., full breath in), and the exhalation is encouraged to be relaxed (i.e., let the breath go). For the breath retention phase, participants are instructed to hold their breath after the 40th *exhale*. The duration of the breath retention is at the discretion of the participant, but the audio recording prompts participants to inhale after approximately 1-, 1.5-, and 2-min for rounds 1–3, respectively, increasing the time of the breath hold each round. Although previous studies on this breathing practice have shown that breath retention was safe up to 3.5 min [47, 48], participants are clearly instructed to inhale when they feel an urge to breathe without forcing it or pushing beyond their limits (i.e., “just inhale when you need”). When the participant inhales to end the breath retention they are instructed to hold their breath again for 10–15 s. This process of deep connected breathing, extended breath retention after an exhale, and brief breath retention after an inhale is considered one round—participants practice three consecutive rounds of this procedure in a single session. In the first Focused-BAT session, the participant practices one round with the researcher to ensure understanding of the instructions before proceeding with the full three rounds. The guided audio recording includes inhale and exhale sounds to pace the breathing during the breathing phase and instructs participants to relax any areas of tightness, tension, or holding and to stay present and pay attention to their body and physical sensations during the breath retention phase (i.e., mindful body awareness).

#### Standard-BAT

Participants are told that the point of the Standard-BAT practice is to remain in an alert and attentive yet relaxed state by taking deep breaths every minute or so [122–124]. The recording first instructs participants to breathe in deeply through their nose for about 5 s and exhale slowly for about 5 s and to continue with this deep breathing on their own for the next minute. Then participants are told to allow their breathing to return to its normal and natural rhythm without trying to change it in anyway, remembering to take a few deep breaths every minute or so. About every minute or two, the audio recording prompts participants to take a couple of deep breaths and includes audible breathing sounds to pace the inhale and exhale. This intervention is designed to be similar in most aspects to the CCBR intervention except with different instructions on how to breathe or how to attend to one’s breathing. Thus, this group can truthfully be told that they have been randomly assigned to a breathing and attention training intervention without actually receiving instructions to bring attention to their body or alter their breathing pattern in a way similar to the CCBR group (i.e., connected breathing, breath holding, mindful body awareness). Previous research has shown this type of breathing and attention intervention decreases pain intensity and pain unpleasantness, but to a lesser degree than a comparable mindfulness meditation training [124] and slow breathing intervention [38]. This Standard-BAT is also expected to be less potent than other deep breathing interventions because there are multiple periods of silence and few instructions on how to breathe, which is in contrast to other interventions that constantly cue participants to breathe deeply and rhythmically [27, 125]. Although some participants may maintain deep breathing on their own, the intervention is intended to induce natural, relaxed, spontaneous breathing.

#### Intervention adherence

At-home intervention adherence will be monitored by collecting data that tracks the length of time a participant stays on the intervention page of the survey that includes the guided audio recording. Specifically, we will assume the intervention was adhered to if a participant stays on the intervention page of the survey for at least 10 min.

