### Statistical analyses

We will assess intervention group equivalence on baseline and outcome variables using relevant univariate tests (chi-square and Kruskal-Wallis) with statistical significance set at *p* < 0.05. Descriptive statistics (percentages, frequencies, means, standard deviations, and 95% confidence intervals) will be used to summarize the results at each timepoint and determine feasibility and acceptability. For feasibility, successful retention is defined as at least 70% of enrolled participants completing the intervention sessions and monthly follow-ups. Acceptability is defined as at least 70% of participants reporting high average ratings (≥ 7 of 10) on acceptability and satisfaction measures. In order to address the secondary objective examining the plausibility of clinical improvement, we will calculate the proportion of participants who report a “moderately important” pain reduction of 30% or greater for each intervention group using the ratings of average pain intensity over the past week. We also plan to explore potential covariates and predictors of treatment response (e.g., age, sex, QST).

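### The 10-minute page-time rule for home adherence is shorter than the 12 minutes of guided breathing, so a session left before the guided part ends can count as adhered

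*Protocol article*

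**What the plan says.** The section on intervention adherence describes a system that "tracks the length of time a participant stays on the intervention page of the survey that includes the guided audio recording", and sets the rule: "we will assume the intervention was adhered to if a participant stays on the intervention page of the survey for at least 10 min". No reason for 10 min is given, and the article describes no second cut-off.

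The section on Breathing and Attention Training defines the session: "Both interventions involve five separate, 17-min practice sessions of BAT". It divides the time in two: "The first 12 min of both interventions include instructions to breathe in ways consistent with their assigned intervention". The rest of the session is a closing silence of 5 min in either arm. Delivery is by a fixed medium: "The interventions will be delivered via an audio recording in order to standardize the interventions across sessions and participants".

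The abstract places two of the five sessions in person and three at home. The section on primary feasibility and acceptability outcomes lists adherence, alongside recruitment, retention and assessment completion, as a rate by which feasibility is judged. The statistical analyses section sets a numerical limit for retention, "at least 70% of enrolled participants completing the intervention sessions and monthly follow-ups", and none for adherence.

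**The concern.** A rule that scores adherence to a recording should not be satisfied before the recording's active content is over. Here the cut-off is below the full session and also below the least demanding content-based standard, which is reaching the end of the guided breathing.

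Adherence is a primary outcome of a pilot whose stated purpose is to supply feasibility estimates and refine the interventions before a larger trial. If early departures are pooled with completed sessions, the rate cannot show how often people working alone stay to the end of the guided part. The logged quantity is also time on a page, not playback, so a page left open without practice already counts. A short cut-off adds to an error that runs mainly towards overstatement.

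**Working it through.** **Inputs.** From Intervention adherence: cut-off 10 min. From Breathing and Attention Training: guided part 12 min, silence 5 min, session 17 min. From Focused-BAT: participants "take about 40 deep connected breaths (no pause between inhale and exhale) at a rate of about 20 breaths per minute"; inhale prompts after about 1, 1.5 and 2 min of retention in rounds 1 to 3; a further hold of 10 to 15 s (0.17 to 0.25 min) after each inhale; three rounds per session.

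**Step 1: reproduce the session length.** 12 + 5 = 17 min, as stated.

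**Step 2: check that the Focused-BAT pacing fits the 12 min.**

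- Breathing: 3 × (40/20) = 6 min.
- Prompted retentions: 1 + 1.5 + 2 = 4.5 min.
- Short holds: 3 × 10 to 15 s = 0.5 to 0.75 min.
- Total: 6 + 4.5 + 0.5 to 0.75 = 11.0 to 11.25 min.

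This fits, with 0.75 to 1.0 min to spare. I assume the spare time is introduction or transitions.

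**Step 3: locate minute 10.** Cumulative times with no introduction:

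| Point in the recording | 10-s holds | 15-s holds |
|---|---|---|
| Round 1 ends | 3.17 min | 3.25 min |
| Round 2 ends | 6.83 min | 7.00 min |
| Round 3 breathing ends | 8.83 min | 9.00 min |
| Round 3 prompted retention ends | 10.83 min | 11.00 min |
| Round 3 ends | 11.00 min | 11.25 min |

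With no introduction, minute 10 falls 10 − 8.83 = 1.17 min or 10 − 9.00 = 1.00 min into the 2-min third retention. If all the spare time comes first, it falls 1.17 − 1.00 = 0.17 min or 1.00 − 0.75 = 0.25 min into it. In every case the recording has not finished round 3.

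**Step 4: compare the cut-off with the content.**

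- Share of the guided part: 10/12 = 83.3%.
- Share of the session: 10/17 = 58.8%.
- Guided time not yet played: 12 − 10 = 2 min.
- Session time not yet elapsed: 17 − 10 = 7 min, or 7/17 = 41.2%.

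The article gives no round-by-round timing for Standard-BAT, but the 12-min guided part applies to both arms, so the 2-min shortfall does too.

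**Step 5: exposure.** The rule applies to 3 of 5 sessions (60%). That is the share of sessions scored this way, not the share misclassified. The latter would need the distribution of page times, which the article does not give.

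**The case against.** The strongest reply is that the rule is openly an assumption, that some cut-off below 100% is a legitimate choice, and that little is lost after 10 min. By then a Focused-BAT participant has been through two full rounds and the breathing of the third. What remains is part of one retention, a short hold and rest. In Standard-BAT the closing minutes are mostly natural breathing with occasional prompts. The Discussion also concedes that fidelity at home cannot be determined.

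Part of this stands. Page time can only ever be a proxy, and the shortfall against the guided part is 2 min. But the concession is about fidelity of home practice and does not explain the value 10. Whether someone stayed on the page until the guided part ended can be read from the durations already collected.

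Four stronger readings are tempting, and the documents do not support them:

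- *The rule inflates the 70% retention criterion.* The statistical analyses section does not say that a 10-min page visit counts as a completed session, and retention and adherence are listed as separate rates.
- *Anyone leaving at 10 min skipped the rest period.* The closing 5 min are silent, and a participant can rest with the page closed.
- *Someone who leaves during the third retention could not tolerate it.* Retention length is left to the participant, so ending it early follows the instructions. Adverse events are also recorded after each session.
- *Only a strict 17-min cut-off will do.* With no tolerance, it would fail a participant who completed the guided part and closed the page seconds early.

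**Conclusion.** The concern holds as a mismatch between the adherence rule and the session it is meant to score. At 10 min, 2 of the 12 guided minutes are still to come in either arm, and the Focused-BAT recording is inside its third retention. Unfinished guided sessions can therefore count towards a primary feasibility rate for the three home sessions. The likely direction is overstatement. The size cannot be given, and no stated success limit is shown to depend on it.

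The round timing rests on pacing that the article calls approximate and on where the spare 0.75 to 1.0 min falls. The main conclusion needs neither, because 10 min is less than the stated 12 min. This is a modest point, worth correcting because correction is cheap.

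**What to change.** 1. Define an adherent home session as at least 12 min on the page, labelled as guided part completed.
2. Also report the proportion staying for about the full 17 min, with a small tolerance stated in advance.
3. State whether the adherence definition is the one used to decide who has completed the intervention sessions in the 70% retention criterion. The article does not currently say.

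If the investigators prefer to keep 10 min, they should give the reason and report the 12-min and full-length rates beside it.

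The change affects scoring only, not the content of the practice, and uses durations already logged. Its cost is that the reported adherence rate may be lower. It does not remove the underlying weakness that a page can be open without practice taking place, so the rate should still be described as a proxy.

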### Assessments and measures

#### Primary feasibility and acceptability outcomes

Feasibility and treatment acceptability are the primary outcomes of the proposed pilot study. Feasibility will be assessed by quantifying rates of participant recruitment, participant adherence, participant retention, and study assessments completion. Treatment acceptability and participant satisfaction will be assessed with several face-valid questions (e.g., How acceptable did you find this BAT treatment? How satisfied are you with this BAT treatment?) rated on a 11-point numerical rating scale (NRS) with anchors that match the content of each question (e.g., 0 = not at all acceptable, 10 = extremely acceptable). These assessments are described further in Additional file 1: Appendix 2 and are similar to those commonly used in other pilot feasibility studies to evaluate the acceptability of an intervention and feasibility of implementing the study protocol [126–131]. In order to capture other aspects of feasibility and acceptability, we will ask participants to answer several open-ended questions about their involvement with the intervention and study procedures more generally (e.g., Were there challenges to participating in this study for you?). No formal qualitative analyses will be conducted, but we will review participant responses to identify possible areas of improvement to the interventions or study procedures [131]. Safety and adverse events will also be recorded after each intervention session using a yes/no symptom checklist and an open-ended prompt for participants to disclose any other possible adverse effects.

#### Baseline assessment and secondary outcomes

Consistent with the purpose of pilot RCTs [100, 117], the additional measures reflect baseline, outcome, and possible process variables that we anticipate will be included in a subsequent efficacy trial [132]. Table 2 indicates the schedule for collecting these psychometrically sound measures, and Additional file 1: Appendix 2 includes more detailed descriptions. The baseline assessment will include demographic and pain and health history questions that align with items recommended by the NIH Task Force on Research Standards for cLBP and the Back Pain Consortium (BACPAC) minimum dataset [119]. Moreover, many of the biobehavioral and patient-reported measures of this study were selected to be consistent with BACPAC recommendations to (1) assess meaningful outcomes following an intervention and (2) include phenotyping measures that may predict who responds to an intervention [158]. Although considered secondary outcomes in the current study, the primary clinical pain outcome measures for a future efficacy trial will be pain intensity and pain interference. The NIH PROMIS pain intensity-short form scale [133] will be used in analyses to determine clinical significance for the proposed study and subsequent efficacy trial by assessing improvements over the last 7 days on average using an 11-point NRS (0 = no pain, 10 = most pain imaginable). Finally, participants will also complete behavioral and physiological assessments at pre- and post-intervention, including physical functioning tasks, quantitative sensory testing, and heart rate variability.

**Table 2 Tab2:** Timeline of study assessments and measures

*Timepoint*	Baseline		Pre-intervention	Post-intervention	Follow-ups		
Variable, category, or measure	Screening	Visit 1	Visit 2	Visit 3	1 months	2 months	3 months
Demographic information	X	X					
Contact information	X						
Eligibility criteria	X	X					
Health history	X	X					
Pain history [119]	X	X					
NIH PROMIS Positive Affect and Well-being [133]		X					
Stress and Adversity Inventory^a^ [134]		X					
Feasibility and acceptability							
Treatment acceptability				X			
Treatment expectations [135]			X				
Blinding effectiveness				X			
Adverse events			X	X			
Secondary outcomes and process measures							
NIH PROMIS-Short forms (pain intensity, pain interference, depression, sleep disturbance, sleep-related impairment) [133, 136–138]		X		X	X	X	X
Brief Pain Inventory-Short form [139, 140]		X		X	X	X	X
Michigan Body Map [141, 142]		X					
Patients’ Global Impression of Change [143–145]				X	X	X	X
Oswestry Disability Index [146]		X		X	X		X
Pain Catastrophizing Scale [147]		X		X	X		X
Pain Self-Efficacy Questionnaire [148]		X		X	X		X
Perceived Stress Scale [149]		X		X	X	X	X
Generalized Anxiety Disorder 2-item [150]		X		X	X	X	X
Multidimensional Assessment of Interoceptive Awareness-2 [151]		X		X	X		X
Multidimensional Psychological Flexibility Inventory^a^ [152, 153]		X		X	X		X
Physical and physiological assessments							
Back performance scale [154]		X		X			
Short performance physical battery [155]		X		X			
Quantitative sensory testing [156, 157]			X	X			
Heart rate variability			X	X			
Oxygen saturation			X	X			
Blood pressure		X	X	X			

^a^Assessment will be completed online between Visit 1 and Visit 2

*NIH* National Institutes of Health, *PROMIS* Patient-Reported Outcomes Measurement Information System

#### Physical functioning assessments

Two tests will be used to assess physical functioning—the Short Physical Performance Battery (SPPB) [155] and the Back Performance Scale (BPS) [154]. The SPPB is a widely used measure of physical function and consists of three tasks: usual gait speed over 4 meters, standing balance, and a chair stand test. The BPS will be used to assess both functional performance and movement-evoked pain through five tasks that are considered difficult for people with cLBP [159, 160]. An assessor will rate physical functioning for participants on each task using a 0–3 scale (total score = 0–15 where higher scores represent worse physical functioning). To measure movement-evoked pain, participants are asked to rate their pain immediately after each task on a 101-point visual analogue scale where 0 = no pain and 100 = most intense pain imaginable.

#### Quantitative Sensory Testing (QST)

We will use QST to determine pain modulatory balance via pressure pain threshold (PPT), temporal summation (TS) of mechanical pain, and conditioned pain modulation (CPM). First, to determine PPT, a handheld pressure algometer with a 1-cm^2^ tip (Medoc, Ltd., AlgoMed, Ramat Yishai, Israel) will be applied to the participants trapezius muscle at a steadily increasing rate of pressure. The participant will press a button when the pressure sensation first becomes painful. This procedure will be repeated five times on the same trapezius muscle, and the mean pressure rating across the five trials will be used for analyses on remote pain sensitivity. Second, to determine remote and local TS of mechanical pain, we will use a 300 *g* nylon monofilament (Touchtest Sensory Evaluator 6.65) to deliver a pinprick sensation to the back of the hand (remote) and lumbar spine (local). A single pinprick stimulus will be delivered and the participant will give a verbal pain rating from 0 (no pain) to 100 (most intense pain imaginable). Then, a series of 10 stimuli (once per second) will be delivered to the same location, and the participant will again give a rating of the greatest pain intensity experienced during the 10 stimuli. This procedure will be repeated twice at each site (back of each hand and bilaterally on lumbar spine) and the trials for each site will be averaged. TS will be used as an indicator of pain facilitation and calculated for each site by subtracting the average rating of the single stimulus from the 10 repeated stimuli. Third, to determine CPM, the test stimulus will be PPT at the trapezius, as described above, and the conditioning stimulus will be immersion of the hand (contralateral to the PPT) in cold water for 1 min at 12 °C (ARCTIC A25 refrigerated bath with an SC150 immersion circulator; ThermoFisher Scientific, USA). PPT will be assessed immediately before cold water immersion, 30 s after immersion, and immediately after withdrawing the hand from immersion. CPM will be used as an indicator of pain inhibition and will be calculated by subtracting the PPT before immersion from the PPT during immersion.

#### Physiological assessments

Physiological data will be recorded throughout the first and last BAT session and summarized across three epochs: 5-min before BAT (resting baseline), 12 min during BAT (active breathing), and 5 min after the BAT practice (recovery) [161]. A Biopac MP150 system with BioNomadix transmitter and RSPEC-R and Oxy100E modules (MP150-BIOPAC Systems Inc., Goleta, CA, USA) will be used for data acquisition, and Biopac’s Acknowledge software will be used for data recording and analyses. We will use a 3-lead EEG, lead II configuration, to record HRV in both the frequency and time domains. A pulse oximeter on the finger of the participant will be used to measure oxygen saturation. To gather baseline data, participants will be asked to lay still for 5 min while reclined before beginning the intervention. Physiological data acquisition will continue throughout the 12-min BAT intervention, and the last 5 min of silence in each intervention will be considered post-test data. Blood pressure will also be measured while the participant is reclined with three continuous readings immediately before the baseline period and after the 5 min of silence. The following physiological parameters will be summarized for each intervention, separated by baseline, during BAT, and post-BAT: Low-frequency (LF), high-frequency (HF), low-to-high frequency (LF/HF), standard deviation of normal-to-normal intervals (SDNN), root mean square of successive differences between heartbeats (RMSSD), oxygen saturation, and blood pressure. We will attempt to schedule Visit 2 and 3 at the same time of day to provide the best comparison of pre-post physiological measures [161, 162].

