The empirical research on conscious connected breathing with breath retention (CCBR) comes from an intervention that is often delivered by a specific teacher (i.e., Wim Hof^1^) within a group retreat setting and combined with additional components (e.g., cold exposure, visualization meditation, strength exercises) [47–50]. These aspects limit accessibility to the intervention and also complicate conclusions that can be drawn regarding the efficacy and mechanisms of the intervention due to the many potential specific and non-specific treatment effects [51–56]. Nevertheless, studies suggest that the breathing and retention practice alone can reduce stress [57] and induce profound physiological changes, including safe respiratory alkalosis (i.e., rise in pH levels), intermittent hypoxia, immediate changes in metabolic and hormonal activity (e.g., increased gluconeogenesis, human growth hormone), and increases in plasma epinephrine levels associated with sympathetic nervous system activation [47–49, 56, 58–60]. CCBR also seems to have significant effects on the immune system, demonstrated by an increase in anti-inflammatory and decrease in pro-inflammatory cytokines following the administration of an endotoxin [48, 56]. Furthermore, the full intervention that included cold exposure and strength exercises was shown safe and feasible for patients with axial spondyloarthritis, a chronic inflammatory disease characterized by pain, with preliminary evidence for reductions in systemic inflammation and disease severity [47]. Yet, CCBR alone has not been tested for its impact on chronic pain, including in those with cLBP.

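### Blood pressure is to be summarised during the breathing practice but is never read then, and its baseline reading comes before the scheduled rest

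*Protocol article*

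**What the plan says.** All the wording at issue is in the Physiological assessments section of the protocol article. Data from the first and last sessions are split into three windows: a 5-min resting baseline, the 12 min of active breathing, and a 5-min recovery. For baseline, "participants will be asked to lay still for 5 min while reclined before beginning the intervention". For recovery, "the last 5 min of silence in each intervention will be considered post-test data".

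Blood pressure has its own sentence. It is taken in the reclined position, and the times given are "three continuous readings immediately before the baseline period and after the 5 min of silence".

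The summary sentence follows directly: "The following physiological parameters will be summarized for each intervention, separated by baseline, during BAT, and post-BAT". Its list holds five heart rate variability indices and ends with "oxygen saturation, and blood pressure".

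Two other places bear on the schedule. The Procedure section says in general terms that physiological data are collected before, during and after practice at Visits 2 and 3, but gives no blood pressure times. Table 2 marks blood pressure by visit only (Visits 1, 2 and 3).

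**The concern.** Two neighbouring sentences do not fit together. One promises a blood pressure summary for the practice window; the other schedules no reading in that window. The arms are meant to differ only in the breathing instructions given in those 12 min, so the missing summary is the one that would show what happens while the arms differ.

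The baseline label is also at odds with the timing. For heart rate variability and oxygen saturation, baseline means the 5 min of lying still. For blood pressure it would mean a reading taken before those 5 min. A results table with one baseline column would show values from two different states without saying so.

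The article calls this pilot a smaller version of the planned trial, to be used to refine procedures. An inconsistency left here is likely to be carried into that trial.

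**Working it through.** No sample size, power or error rate is involved, so the check is a timeline and a count.

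**Inputs** (Physiological assessments, unless stated)
- Windows: 5 min baseline, 12 min practice, 5 min silence.
- Blood pressure times: just before the baseline window, and after the silence.
- Parameters listed: LF, HF, LF/HF, SDNN, RMSSD, oxygen saturation, blood pressure, so 7.
- Order of sensory testing and practice at each visit: Procedure section.
- Content of sensory testing, including hand immersion at 12 °C for 1 min: Quantitative Sensory Testing section.

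**Step 1. Timeline of a recorded session**

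Blood pressure → 5 min baseline → 12 min practice → 5 min silence → blood pressure.

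Minimum scheduled time between the two sets of readings: 5 + 12 + 5 = 22 min.

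**Step 2. Readings set against the promised summaries**

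| Promised summary | Defined window | Blood pressure reading in the window |
|---|---|---|
| Baseline | 5 min of rest before BAT | None; the reading is taken before the window opens |
| During BAT | 12 min of practice | None, and none adjacent to it |
| Post-BAT | 5 min of silence | None; the reading is taken after the window closes |

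There are two measurement occasions for three summaries. Taken strictly, neither lies inside a defined window. Taken loosely, the first can stand for baseline and the second for post-BAT, but nothing can stand for during BAT. Each arm and visit has 7 × 3 = 21 promised summaries, and 1 of the 21 cannot be derived. Over two visits and two arms that is 4 of 84.

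**Step 3. Comparison within a session**

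The first set of readings comes before the scheduled 5-min rest. The second comes at least 22 min later, directly after 5 min of silence. A difference between them therefore contains whatever change comes from settling as well as any change from the practice, and the schedule gives no means of separating the two. The times are the same for both arms, so the settling part is expected to be common to both and to cancel in a between-arm contrast.

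**Step 4. Comparison between visits**

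| | Visit 2 | Visit 3 |
|---|---|---|
| Sensory testing relative to practice | Before | After |
| Rest scheduled between sensory testing and the pre-session reading | None stated | Not applicable |

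On the order given, the pre-session reading at Visit 2 follows painful stimuli and cold-water immersion, and the one at Visit 3 does not. Pre-session readings are therefore not taken under like conditions at the two visits.

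**The case against.** The strongest defence is that this is a drafting slip. One sentence covers seven parameters, six of them recorded continuously, and blood pressure was added without an exception. Much of that stands: the likely intention was a before-and-after reading, and deleting a few words removes the contradiction. But the article gives both the measurement times and the summary windows, and they conflict, so condensation from a fuller protocol does not explain it.

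A second defence is that the article defines no within-session change in blood pressure, and that the only physiological pre-post comparison it names is Visit 2 with Visit 3, where readings at the same point of the session can be compared. The first half is right, so the settling problem applies only if the baseline and post-BAT columns are read against each other. The second half does not hold for the pre-session reading, because of the order of sensory testing.

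A third is practical. The present timing keeps the cuff out of every recording window, and a reading between practice and silence would interrupt a continuous 17-min audio session just as the recovery window opens. That is a good reason not to ask for a mid-session reading, and the fix below does not.

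A reader might go further and infer that the schedule pushes the change towards a fall and so hides a safety signal, given that the Background reports "increases in plasma epinephrine levels associated with sympathetic nervous system activation" and that people above 150/95 are excluded. The documents do not support that. The Background statement summarises earlier studies and predicts no pressure rise here. The 150/95 limit is an eligibility rule. Adverse events are collected by symptom checklist and open prompt after each session, and Table 2 lists blood pressure under physical and physiological assessments, apart from adverse events. No conclusion about the presence or absence of a rise is planned, and nothing in the article allows one to say how much of any rise would remain after the silence.

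**Conclusion.** The point holds within limits. The during-BAT blood pressure summary cannot be derived from the schedule, and the baseline reading lies outside the window that defines baseline for the other parameters. Both follow from the text and need no assumption.

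The remaining consequences are conditional. A baseline to post-BAT comparison within a session would mix settling with the breathing effect, by an amount the documents do not let one estimate. The article does not say how long participants have been reclined before the first readings, so those readings can be described only as taken before the scheduled rest. The Visit 2 to Visit 3 comparison of pre-session readings is affected by the order of sensory testing, assuming the visits run in the order the Procedure section gives.

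No between-arm bias is shown from settling. This assumes that the single rehearsal round in the first Focused-BAT session, which the article does not place relative to the readings, leaves the timing in the two arms alike.

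No primary outcome, feasibility criterion or sample-size figure depends on blood pressure. The passage is wrong as written and cheap to put right, but it does not threaten the aims of the pilot.

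**What to change.** 1. Move the three pre-session readings to the point after the 5-min reclined baseline recording has ended and before any BAT breathing begins, including the rehearsal round in the first Focused-BAT session. Pre- and post-session readings then each follow 5 quiet minutes, and the scheduled time between them becomes 12 + 5 = 17 min. At Visit 2 a fixed rest separates sensory testing from the reading, although the difference in visit order remains and should be noted when the visits are compared. The cuff stays outside the heart rate variability window.
2. Limit the three-window summary to heart rate variability and oxygen saturation. Summarise blood pressure as pre-session and post-session only, and state that its response during practice is not assessed.

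The cost is two edited sentences and a short delay before the audio starts at each of two visits, with no new equipment and no extra readings. The second change costs nothing and can be made at any stage. If some participants have already been measured under the present timing, record when the first change took effect and do not pool pre-session readings across it without saying so.
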